## Abstract

**Background:**

Recently, a large group of patients with persistent dyspnea, poor physical capacity, and reduced health-related quality of life (HRQoL) following pulmonary embolism (PE) has been identified and clustered under the name “post pulmonary embolism syndrome” (PPS). These patients seem good candidates for pulmonary rehabilitation. The aim of the study is to explore whether a pulmonary rehabilitation program can improve physical capacity, dyspnea, and HRQoL in PPS patients.

**Methods:**

A two-center randomized controlled trial (RCT) is being performed at Østfold Hospital and Akershus University Hospital in Norway. Patients with PPS are 1:1 randomized into an intervention or a control group. The intervention consists of a supervised, outpatient rehabilitation program twice weekly (1 h) for 8 weeks provided by experienced physiotherapists. The intervention involves individually adapted exercises based on existing pulmonary rehabilitation programs (relaxation, interval, and resistance training), and an educational session including topics such as normal anatomy and physiology of the respiratory and circulatory system, information on PE/PPS, breathing strategies, and benefits of exercise/physical activity. Patients randomized to the control group receive usual care without specific instructions to exercise.

Participants in the intervention and control groups will be compared based on assessments conducted at baseline, 12 weeks, and 36 weeks after inclusion using the incremental shuttle walk test (primary outcome) and endurance shuttle walk test (exercise capacity), Sensewear activity monitor (daily physical activity), the modified Medical Research Council scale, the Shortness of Breath Questionnaire (dyspnea), and EQ-5D-5L and the Pulmonary Embolism Quality of Life Questionnaire (HRQoL).

Recruitment of 190 patients is currently ongoing.

**Discussion:**

Results from this study may provide a currently untreated group of PPS patients with an effective treatment resulting in reduced symptoms of dyspnea, improved exercise capacity, and better HRQoL following PE.

**Trial registration:**

Clinical Trials NCT03405480. Registered prospectively on September 2017.

Protocol version 1 (from original protocol September 2017).

The study protocol has been reported in accordance with the Standard Protocol Items: Recommendations for Clinical Interventional Trials (SPIRIT) guidelines (Additional file 1).

## Background

Pulmonary embolism (PE) occurs when an emboli blocks a pulmonary artery resulting in acute symptoms, such as dyspnea and chest pain, which usually subside gradually with the majority of patients regaining normal function within 3–6 months [1]. However, long-term complications following PE can include recurrent venous thromboembolism (VTE), bleeding, and chronic thromboembolic pulmonary hypertension (CTEPH) [2, 3].

Several studies have shown that up to 50% of patients complain of various grades of persistent unexplained dyspnea many years after the diagnosis of PE [4, 5]. Furthermore, patients who reported dyspnea had reduced exercise capacity as measured by the 6-min walk test (6MWT) compared to patients with no dyspnea [6]. Additionally, those suffering from persistent dyspnea had impaired health-related quality of life (HRQoL) compared to both the normative population and PE patients without dyspnea [4]. These findings have recently been confirmed by a prospective study showing that half of PE patients have an exercise limitation at 1 year post-PE which negatively influences walking distance and reduces HRQoL [7]. Some of these patients have persistent pathological findings, such as right ventricular dysfunction, pulmonary hypertension, or residual perfusion defects causing dead space ventilation, which may explain, at least in part, the persistent symptoms. The majority of patients, however, have no detectable cardiopulmonary sequel and merely suffer from deconditioning. Foregoing research has led to the recognition of patients with the so-called post-PE syndrome (PPS), defined as new or progressive dyspnea, exercise intolerance, and/or diminished functional status following PE without an apparent non-PE alternative explanation [8]. Guidelines provide clear recommendations for the management of CTEPH, the most severe presentation of PPS affecting about 4% of the patients following PE [2]. Studies focusing on adequate treatment of other PPS presentations to improve functionality and decrease symptoms are, however, lacking and guidelines make no mention of this large patient group. Because it is likely that physical deconditioning may be responsible for at least a part of the disease burden, it has been hypothesized that patients with PPS may benefit from pulmonary rehabilitation [7, 9].

Pulmonary rehabilitation is a core component in the management of chronic lung disease and is mostly utilized by patients with chronic obstructive pulmonary disease (COPD). Programs typically consist of patient-tailored therapies such as exercise training, education, and behavioral changes, based on a thorough assessment of the patient, with the goal of improving physical and psychological condition and promoting long-term adherence to health-enhancing behaviors [10]. Rehabilitation is a cost-effective intervention and has demonstrated a reduction in respiratory symptoms such as the perception of dyspnea, improved physical function and HRQoL in patients with COPD, and reducing hospital admissions and improving mortality rates [10]. Recently, there has been an increased focus on the benefits of rehabilitation for other types of patients experiencing similar respiratory symptoms and reduced exercise capacity, such as lung cancer, pulmonary hypertension, and cystic fibrosis [10]. Moreover, a study from 2016 investigated the feasibility of a breathlessness rehabilitation program for patients with both respiratory and cardiac disease suggesting that rehabilitation should focus on the symptoms and limitations that patients experience rather than traditional disease-focused rehabilitation [11].

To our knowledge, there are few studies that have addressed the effect and safety of rehabilitation and exercise after PE or DVT. One retrospective study evaluated the safety of rehabilitation after PE, showing that it is safe to start to exercise following PE [12]. One small randomized controlled trial (RCT) objectively measured the effect of exercise and behavioral weight loss after VTE demonstrating that early initiation of exercise was safe and resulted in improvements in physical activity and fitness [13]. Both studies pointed out the need for large prospective RCTs. Furthermore, a recently completed study randomized patients with newly diagnosed PE, regardless of the presence of persistent dyspnea, to a home-based training program or a control group [14]. This study concluded that home-based exercise training and nurse consultations did not improve exercise capacity or symptoms of dyspnea following PE. However, this study included all PE patients, rather than those with PPS only, thus including patients who had recently been diagnosed with PE where a spontaneous improvement in symptoms can be expected from the natural course of the disease. No current studies have provided rehabilitation to patients suffering with PPS. Previous research has indicated that the HRQoL impairment in patients with PPS is driven by reduced physical capacity [4] suggesting a possible receptivity for an intervention such as pulmonary rehabilitation, including exercise training, in order to reduce breathing discomfort and improve HRQoL and exercise capacity.

The aim of this study is to explore the effect of pulmonary rehabilitation on exercise capacity, dyspnea, and HRQoL in patients with PPS.

### Hypothesis

The primary hypothesis is that a structured, outpatient, hospital-based, 8-week pulmonary rehabilitation program will lead to increased exercise capacity, less symptoms of dyspnea, and improvements in HRQoL in patients with PPS as compared to a control group receiving no active intervention.

## Methods and design

### Study design

A two-center RCT is being performed at the outpatient departments of Østfold Hospital Trust (ØHT) and Akershus University Hospital (AHUS) in Norway. Patients with PPS are 1:1 randomized into two arms, an intervention arm and a control arm, using sealed envelopes. The allocation sequence will be computer generated, and to ensure balanced recruitment during the study, this will be performed in blocks of 10. The allocation sequence will not be available to the person enrolling participants and the randomization code will be kept inside sealed opaque envelopes. The generation of the allocation sequence has been performed by the statistician at ØHT. The enrollment process and assignment of interventions will be performed by the PhD candidates.

In addition, a group of patients with no PPS following PE will be examined at baseline to compare patients with and without persistent dyspnea after PE in terms of exercise capacity, daily physical activity, dyspnea, and HRQoL.

The primary study objective is to explore the short-term changes in exercise capacity from baseline to 12 weeks after inclusion between groups as measured by the incremental shuttle walk test (ISWT). The secondary objectives are to explore the long-term effect of the rehabilitation program on exercise capacity 36 weeks after inclusion between groups (ISWT) as well as changes in exercise endurance (ESWT), subjective symptoms of dyspnea, daily physical activity levels, and HRQoL from baseline to 12 and 36 weeks after inclusion.

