### Blinding

The investigators performing the walking tests at follow-up are blinded to the patients’ group allocation. Due to the nature of the intervention, blinding of the participants and the physiotherapists providing the intervention is not possible. The statistician who will perform the data analysis will be blind to group allocation.

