### Data monitoring

The study will be monitored by the research department at ØHT. Any adverse effects will be reported. The trial steering committee is made up of the supervisors of the three PhD candidates and a selection of experts within the field of PE. The role of the steering committee is to ensure the quality of the trial and sufficient progress underway. The trial steering committee will meet twice a year to review the progress of the study and address potential challenges and obstacles during the course of the trial. The PhD candidates are responsible for setting up the committee meetings. The group providing day to day support for the progression of the trial is made up of the PhD candidates and their main supervisors, as well as research nurses and research advisors at ØHT who ensure the performance of the trial and practical tasks such as testing patients following intervention (blind to randomization). The PhD candidates are responsible for all aspects of local organization including identifying potential recruits and collecting informed consent. The PhD supervisors and advisors at the research department at ØHT are responsible for supervising the trial and meet regularly. As this trial does not involve any use of pharmaceutical drug or medical device, no formal safety and monitoring board has been established. However, the conduct and progress of the study will be regularly overseen by the leader of the group, professor [name].

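### One published block size of 10, operated by the staff who recruit, consent and assign, leaves up to one allocation in six deducible

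*Protocol article*

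**What the plan says.** Study design in the protocol article sets out the randomisation: "Patients with PPS are 1:1 randomized into two arms, an intervention arm and a control arm, using sealed envelopes". The sequence is computer generated, and "to ensure balanced recruitment during the study, this will be performed in blocks of 10". No other block size is given.

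Three safeguards are stated in the same section: "The allocation sequence will not be available to the person enrolling participants"; "the randomization code will be kept inside sealed opaque envelopes"; and "The generation of the allocation sequence has been performed by the statistician at ØHT".

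On who operates the scheme, Study design says "The enrollment process and assignment of interventions will be performed by the PhD candidates", and Data monitoring adds that "The PhD candidates are responsible for all aspects of local organization including identifying potential recruits and collecting informed consent". Blinding says that participants and treating physiotherapists cannot be blinded, whereas the follow-up walk testers and the analyst are. The Abstract and Trial status show that recruitment was still open when the article appeared. Trial status also shows that ØHT recruited alone from January 2018 until AHUS joined in August 2019.

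**The concern.** Concealment has two parts: nobody who enrols may see the list, and nobody who enrols may be able to work it out. The stated safeguards deal with the first. The second is weak when the block size is constant and known, because each block must finish with five patients per arm. Whoever opens the envelopes learns each allocation, and here the same people decide whom to approach and enrol next.

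Eligibility leaves some room for judgement. Dyspnoea must have begun or become worse since the embolism, and a patient may be excluded for a condition expected to hinder compliance. A patient could be deferred or declined without an evident protocol breach. If knowledge of the next arm influenced such decisions, the arms would differ at entry. Blinded walk tests protect the measurement, and intention-to-treat analysis protects the comparison after randomisation. Neither repairs selection before it.

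**Working it through.** The plan gives no figure for predictability, so this is a direct calculation.

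**Inputs.** Block size 10 and ratio 1:1, so five per arm (Study design). Total 190 (Sample size calculation): 86 per arm × 1.10 = 94.6, rounded up to 95, and 2 × 95 = 190. That is 190/10 = 19 blocks.

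**Certain allocations.** A block has C(10,5) = 252 equally likely orders. The allocation at position i is certain if one arm has already used its five places, which has probability 2 × C(i−1,5)/252:

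- positions 1 to 5: 0
- position 6: 2/252 = 0.8%
- position 7: 12/252 = 4.8%
- position 8: 42/252 = 16.7%
- position 9: 112/252 = 44.4%
- position 10: 252/252 = 100%

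The sum is 420/252 = 1.67 per block, or 16.7%. Over 19 blocks, 19 × 1.67 ≈ 32 of 190.

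**Best guess.** Always naming the arm that is behind gives, with m = 5, an expected m + (2^(2m)/C(2m,m) − 1)/2 = 5 + (1024/252 − 1)/2 = 6.53 correct of 10. That is 65.3%, against 50% by chance.

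**What the bound needs.** The recruiter must know the block size and hold a complete tally. Suppose instead that two centres draw from one list, and a recruiter sees only local allocations but knows where each block starts. Simulation then gives certainty for 5.4% of that recruiter's patients if 80% of patients are local, and 0.5% if 50% are local. Best-guess success is 60.6% and 56.7%. Both shares are assumptions, because the article gives no split by centre.

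**Other fixed sizes.** The certain share of a fixed block of size 2m is 1/(m+1): 33% at size 4, 25% at 6, 20% at 8 and 16.7% at 10. A smaller fixed block would be worse.

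**Randomly varying sizes.** These were simulated for a recruiter who knows the set of sizes and every past allocation, but not the order of the sizes. The last column is the certain share applied to all 190 patients.

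| Sizes | Certain | Best guess | Certain of 190 |
|---|---|---|---|
| 10 only | 16.7% | 65% | about 32 |
| 4, 6, 8 | 2.0% | 68% | about 4 |
| 6, 8, 10 | 1.5% | 66% | about 3 |
| 8, 10, 12 | 1.1% | 65% | about 2 |

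**Scale of possible bias (illustration only).** Assume that every certain place was exploited and that the patients in those places differed between arms by 30 to 60 m in walk-test change. The bias would be 0.167 × 30 = 5 m to 0.167 × 60 = 10 m, against the 60 m that the plan treats as clinically relevant.

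**The case against.** The strongest reply is that the article describes real safeguards: a statistician-generated list, withheld from the enroller and kept in opaque sealed envelopes. Ten is also less predictable than the smaller fixed blocks often used, and about five in six allocations are never certain. The deduction needs a running tally across up to three PhD candidates, and no section says that anyone keeps one. Nor does the article say that the candidates knew the block size before publication, which came after AHUS had started. All of this stands, and it makes 32 of 190 a ceiling. It does not remove the point: the size is now public, and hiding the list does not prevent deduction from opened envelopes.

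Stronger readings are tempting, but the documents do not support them:

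- A reader might blame predictability on the absence of stated stratification by centre. The effect runs the other way: a shared list lowers predictability once both centres recruit, whereas centre-specific fixed blocks of 10 keep the full 16.7% in each. A condensed article may also simply omit stratification.
- A reader might expect a serious imbalance of arms within the second centre. The article gives neither its patient number nor the list structure, and AHUS patients can come only from places filled after August 2019. No figure can be supported.
- A reader might infer that the analyst is unblinded because a statistician at ØHT made the list. The article does not say that this is the same person, and Blinding states that "The statistician who will perform the data analysis will be blind to group allocation".

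**Conclusion.** The point holds as a moderate, conditional risk of selection at entry, arising from one disclosed block size together with recruitment and assignment in the same hands. The upper bound is 16.7% of allocations. The complete tally is most plausible for the roughly 19 months when ØHT recruited alone, provided the candidates already knew the size, or for any period if the lists are centre-specific. With one shared list and only local knowledge, the share is lower, at about 0.5% to 5% under the assumed splits. Nothing in the article suggests that any allocation was predicted or misused. The change is worth making because it is cheap and can still protect the patients not yet randomised.

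**What to change.** For the envelopes not yet used, the statistician reissues the sequence in randomly varying block sizes, for example 6, 8 and 10, with neither the sizes nor their order disclosed to the enrolling staff. The next numbered envelope is opened only after eligibility, consent and baseline tests have been recorded. If separate lists per centre are used, varying the sizes is essential.

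This lowers certain allocations from 16.7% to about 1-2% of those still to be made (about 2-4 if applied to all 190). Envelopes already opened are unaffected. The best-guess rate does not improve, so the change should be justified by the removal of certainty alone.

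The cost is a short amendment and a reissued envelope set during recruitment, and a block may be left incomplete at the switch.

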### Eligibility criteria

Patients diagnosed and treated for PE 6 months to 6 years previously at ØHT or AHUS are identified from ØHT’s Thrombosis registry (TROLL registry—NSD 28435/3/LMR) (ØHT only) or via ICD-10 discharge codes (AHUS). Patients are invited to participate by postal mail.

Inclusion criteria include age 18–75 years, objectively diagnosed symptomatic PE (greater than isolated sub-segmental PE) by CTPA 6 months to 6 years prior to inclusion to the study, persistent dyspnea defined as modified Medical Research Council (mMRC) breathlessness scale grade ≥ 1 that had appeared or worsened after the diagnosis of PE, and the ability to provide written informed consent.

Exclusion criteria include pulmonary diseases (such as COPD GOLD ≥ 2 or restrictive pulmonary diseases, lung cancer, or pleural disease), heart failure, CTEPH, significant valvular heart disease, patients with a condition that would interfere with the ability to comply with the study protocol or to give informed consent (e.g., history of drug abuse, excessive alcohol beverage consumption, cognitive dysfunction, or severe psychiatric disease), active malignancy or recurrent, metastatic or inoperable disease, life expectancy less than 3 months, and pregnancy.

### Blinding

The investigators performing the walking tests at follow-up are blinded to the patients’ group allocation. Due to the nature of the intervention, blinding of the participants and the physiotherapists providing the intervention is not possible. The statistician who will perform the data analysis will be blind to group allocation.

### Intervention

#### Rehabilitation group

Patients in the intervention group are allocated to a basic pulmonary rehabilitation program consisting of a supervised, outpatient exercise program for 1 h twice weekly for 8 weeks. Experienced physiotherapists construct an individually adapted exercise program based on existing pulmonary rehabilitation programs (combining relaxation, interval training at moderate intensity measured with the Borg scale, and resistance training), and an educational session provided by a medical doctor and a physiotherapist. The educational session includes topics, such as normal anatomy and physiology of the respiratory and circulatory system, information on PE and PPS, breathing strategies, and benefits of exercise/physical activity. Training attendance is documented and patients will be given a simple home-based exercise program, consisting of resistance exercises that can be performed without equipment, to be performed once to twice weekly during the intervention period. Implementing supervised, outpatient rehabilitation program will not require alteration to all other usual care pathways (including use of any medication in particular anticoagulation) and these will continue for both trial arms. Minimal actions will be made to improve adherence, for example only one telephone call will be made in the case of poor attendance.

#### Control group

Patients randomized to the control group will receive usual care without specific instructions to exercise (no active intervention). All patients were treated and followed up according to international guidelines [15]. The participants randomized to standard care in the control group will not receive any structured exercise or information as part of the current study, but continue their routine follow-up at the outpatient clinic. However, if they already perform regular physical activity at the time of inclusion, they are encouraged to continue doing so.

### Outcome measures

#### Primary outcome measure

The primary endpoint of the study is improvement in physical capacity as measured by the ISWT. This walking test has been developed to assess exercise capacity and is valid, reliable, and responsive in a number of study populations, including patients with cardiac and respiratory diseases [16]. The patient walks between two shuttles along a 9-m track in a tempo guided by audible sounds which increase in speed every minute for a maximum of 12 min. The test ends when the patient cannot manage to keep the correct speed or has to stop because of symptoms (such as dyspnea or fatigue). Standardized instructions will be provided before the test commences. In order to exclude a learning effect, the ISWT is performed twice at baseline with at least 15 min between tests. Peripheral oxygen saturation is registered and patients will report their subjective experience of dyspnea during exertion using the Borg scale before and immediately after the test [17]. The Borg scale is commonly used for assessing perceived exertion during field walk tests. The minimal clinical important difference (MCID) for the ISWT is 70 m in patients with cardiac disease and 48 m in patients with COPD [18, 19].

